### Secondary outcome:

A similar analysis will be conducted for the secondary outcomes of all playground injuries and of head injuries. Fractures will be reanalyzed varying the severity threshold to consider only displaced fractures requiring reduction.

### Data Collection, Handling, Computerization and Analysis

Faxed copies of OSBIE incident reports will be sent from the school to the research assistant at the Hospital for Sick Children. The research assistant will then contact parents by letter to inform them of the study and then by telephone (evening where necessary) to obtain verbal consent to participate in the study. The CHIRPP form and appendix will be used to collect specific information regarding the injury. HSC telephone interpreter services will be used where necessary if English is not the first language. Faxed copies of emergency room or inpatient discharge sheets will be sent to the research assistant at HSC and will be coded using ICD 10 codes for diagnosis and procedures. A secure trial database will be maintained at The Hospital for Sick Children using ACCESS software. Completed data will be exported from ACCESS for analysis in SAS-PC.

## Are there any planned subgroup analyses?

Because the effect of the surface may be different in wet versus dry conditions, or in frozen versus thawed conditions, analysis by weather and by season will be undertaken. For analysis by weather, the data will be split into wet days (>= 2mm rainfall) and dry days and the analysis above will be repeated in each set. For analysis by season, the data will be split into winter (Dec 21 to March 21) and not winter (all other dates) and the analysis above will be repeated in each set.

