**Rationale:** Loose fill playground surfaces are popular because they are an inexpensive way of meeting impact attenuation standards. Physical and epidemiological studies suggests that fractures may occur more often on higher friction fills (wood fibre) and less often on lower friction fills (sand), but the surfaces have never been compared using injury rates as an outcome. Real world performance of the surface will also depend on its behaviour in wet, frozen, or snowy conditions and on how children play in that particular surface. The most meaningful test of effectiveness of a surface is injury rates during real world use. A unique opportunity exists to perform a randomized trial which will guide standards development and allow evidence based injury prevention. This is the first randomized trial of a playground injury prevention intervention, is methodologically unique, and will lead directly to improved standards and improved health.

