### Covariates

School population, playground size, socioeconomic status, and number of hours of play may influence injury rates although such effects would be independent of surfacing so it is simply necessary to balance the groups. The randomization has already been performed and school population, playground size, and socioeconomic status are balanced as would be expected with 37 clusters (see table 1 in sec 2.3). At each school, supervised outdoor play occurs for equal mandated time periods (totaling 2 hours) each day, weather permitting. Intensity of supervision will be addressed by calculating the student to teacher ratio at each school according to the playground supervision roster.

Weather will be the same for all schools, but it is possible that effect modification (different injury risks by surface in wet vs dry weather, or when frozen) could occur. Accordingly, rainfall and snowfall amounts will be recorded from Environment Canada web records and will be used in a secondary analysis as described below.

Depth of undersurface measurements will be done three times per year (September, January and June) of surfaces at all schools at falling points and slide exits. Falling heights will be recorded by surveying the equipment using diagrams and digital photos, and asking parents for the location of any injury fall. Depth measurements and falling heights will be used as covariates in the analyses (see appendix).

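### The wet/dry split ignores the snowfall the protocol says it will use, and the frozen/thawed question is answered by calendar dates, so the weather subgroup contrasts are diluted.

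*Protocol*

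**What the plan says.** The rationale in the protocol section What is the problem to be addressed? states: "Real world performance of the surface will also depend on its behaviour in wet, frozen, or snowy conditions". The Covariates section raises the same question for the analysis: "it is possible that effect modification (different injury risks by surface in wet vs dry weather, or when frozen) could occur". It then commits to data: "rainfall and snowfall amounts will be recorded from Environment Canada web records and will be used in a secondary analysis as described below".

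The only description that follows is in Are there any planned subgroup analyses? Its stated reason opens: "Because the effect of the surface may be different in wet versus dry conditions, or in frozen versus thawed conditions, analysis by weather and by" (the sentence goes on to name season). Two rules are set. The wet/dry rule is: "the data will be split into wet days (>= 2mm rainfall) and dry days and the analysis above will be repeated in each set". The season rule is: "the data will be split into winter (Dec 21 to March 21) and not winter (all other dates".

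Neither rule contains a snowfall or temperature term. The Covariates section also states: "Weather will be the same for all schools".

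**The concern.** The protocol names three surface conditions of interest: wet, frozen and snowy. The two rules capture only rain on the day and the date.

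- **Snow.** Snowfall is to be collected for this analysis but has no role in it. A day with snow and under 2 mm of rain goes into the dry group.
- **Frost.** The frozen/thawed question is the stated reason for the split, but the split is a calendar window. A frozen day on 10 December or 28 March counts as not winter, and a thawed day in February counts as winter.

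The protocol itself gives grounds to expect effect modification. It reports that wood fibre attenuates impact better than sand when wet or frozen, and that sand is softer and lower in friction. If the surface effect does change with condition, mixing conditions within a group pulls the group results together. The trial could then report that weather makes little difference partly because of how days were sorted. The results are intended for a revision of the national playground standard, so that message would carry weight.

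**Working it through.** **1. The passages side by side**

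| Condition named in the protocol | Rule that should capture it | Where such days fall |
| --- | --- | --- |
| Wet | Rainfall of 2 mm or more | Wet |
| Snowy, under 2 mm rain | None, though snowfall is recorded | Dry |
| Frozen, inside Dec 21 to March 21 | Calendar window (91 days, both ends included) | Winter |
| Frozen, outside the window | None | Not winter |
| Thawed, inside the window | None | Winter |

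The snow error runs one way: it puts snow days into dry and no dry days into wet. The season rule can err both ways.

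**2. How much dilution (illustration only)**

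The documents give no share of wet, snowy or frozen days, so every input in this step is an assumption. Let the true sand:fibre rate ratio be 1.0 in the affected condition and 0.5 otherwise, a true ratio of ratios of 2.0. Let p be the share of reference-arm fractures in the affected condition (0.3 to 0.5), s the share of those that the rule catches, and sp the share of the remaining fractures that it files correctly. The same values apply in both arms.

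- Filed as affected: [p·s·1.0 + (1−p)(1−sp)·0.5] / [p·s + (1−p)(1−sp)]
- Filed as unaffected: [p(1−s)·1.0 + (1−p)·sp·0.5] / [p(1−s) + (1−p)·sp]

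Example with p = 0.4, s = 0.7, sp = 1: the dry ratio is (0.12 + 0.30)/(0.12 + 0.60) = 0.58, the wet ratio stays at 1.0, and the contrast is 1.0/0.583 = 1.71.

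| s | Dry ratio, sp = 1 (true 0.50) | Contrast, sp = 1 | Contrast, sp = 0.95 |
| --- | --- | --- | --- |
| 90% | 0.52–0.55 | 1.83–1.92 | 1.78–1.81 |
| 70% | 0.56–0.62 | 1.62–1.80 | 1.56–1.66 |
| 50% | 0.59–0.67 | 1.50–1.70 | 1.42–1.53 |
| 30% | 0.62–0.71 | 1.42–1.62 | 1.30–1.39 |

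The sp = 1 columns match the snow error in the rain split. The last column illustrates a rule that errs both ways, as the season split can.

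**3. How many fractures the subgroups hold**

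Inputs from Primary Outcome Measure under the sample size heading: λ0 = 0.004 and λ1 = 0.002 per student-year, y = 820 student-years per school, k = 0.2, alpha 0.05 (taken as two-sided), power 80%.

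The plan's own figure reproduces: c = 1 + (1.96 + 0.84)² × [(λ0+λ1)/y + k²(λ0²+λ1²)]/(λ0−λ1)² = 1 + 7.85 × (7.317×10⁻⁶ + 0.8×10⁻⁶)/(4×10⁻⁶) = 16.93, that is 17 per arm.

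With 37/2 = 18.5 schools per arm, expected fractures are 18.5 × 820 × 0.004 = 61 and 18.5 × 820 × 0.002 = 30. Inverting the formula with y replaced by 820·f, for a stratum with an assumed share f of exposure:

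| f | Expected fractures | Power for a halving |
| --- | --- | --- |
| 10% | 6 vs 3 | 16% |
| 20% | 12 vs 6 | 28% |
| 30% | 18 vs 9 | 38% |

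**The case against.** The strongest reply is that these are exploratory subgroups with sound external modifiers. Rain and date cannot be affected by the allocated surface, and the protocol takes weather as equal across schools, so each stratum remains a randomized comparison for its day type. The section speaks of analysis by weather and by season and does not claim to measure surface state. Sparse counts limit the analysis at least as much as the definitions do, and finer categories thin the data further. All of this stands. It limits the size of the point but does not explain why snowfall is collected for an analysis that does not use it, or why a frozen/thawed question is put to a calendar.

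It may also be said that day coding belongs in a statistical analysis plan. Here, however, the protocol has itself fixed the threshold and the dates.

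Three stronger readings are tempting but not supported:

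- **The weather question cannot be answered.** The illustration shows a contrast pulled toward 1, not removed.
- **Both rain strata are contaminated.** The snow error affects only the dry group.
- **Most wet-surface play is labelled dry because surfaces stay wet overnight and rain cancels play.** If 20% of days are rainy, 30% of rain days follow a rain day and wetness always lasts into the next day, 0.14/0.34 = 41% of wet-surface play days are mislabelled. If only a quarter of rain-day play goes ahead, the figure is 0.14/0.19 = 74%. None of these inputs is in the documents. The protocol describes sand as fast-draining and the wood fibre system as including a drainage layer. It says that play occurs "supervised outdoor play occurs for equal mandated time periods (totaling 2 hours) each day, weather permitting", but gives no figure for lost play.

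**Conclusion.** The point holds as a mismatch between the stated question and the stated rules. The snowfall part rests on the text alone. The frozen/thawed part rests on the absence of any temperature criterion in the split. The weather data named are rain and snow amounts; the appendix with the added interview questions is not shown, so it cannot be said that no record at all would identify a frozen day.

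The consequence is modest: a contaminated dry group, a season split that mixes frozen and thawed days on both sides, and so a weakened contrast in analyses that already have few events. There is no bias between arms and no effect on the primary analysis.

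The size is illustrative only. It assumes that snow shifts the surface effect in the same direction as rain. If it does not, the dry group is still mixed, but the direction of the error is not fixed.

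**What to change.** In Are there any planned subgroup analyses?:

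1. Give the recorded snowfall a role: take snow days out of the dry group, either as their own category or combined with rain as wet/snow.
2. Define frozen versus thawed days by daily temperature from the same Environment Canada records, with the cut-off stated in advance. Keep the Dec 21 to March 21 split as descriptive. This assumes that the source supplies daily temperature, which the protocol does not say.
3. Apply the same day types to the student-time denominator, so that stratum rates refer to the exposure in that stratum.
4. If temperature is not added, call the season split a calendar-season analysis and drop the frozen/thawed interpretation.

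Counting rain on the previous day as wet is an optional sensitivity analysis. These definitions use external weather, which the surface cannot influence, so they do not condition on anything that follows randomization.

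The cost is a few sentences, one further weather column and slightly more data handling. The downside is smaller strata in an already low-count analysis; a combined wet/snow category limits this.

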## What is the proposed frequency of analyses?

The final analysis will be performed at the completion of the trial.

## Will the trial address any economic issues?

A cost-benefit analysis will be conducted from the Ontario provincial government perspective since both direct health care costs and education funding fall under the jurisdiction of the provincial government.

Direct health care costs will be calculated from OHIP perspective as follows: a) no visit – no cost. b) physician office visit only – GP minor assessment fee. c) emergency department visit – visit cost for ‘average’ Ontario ED visit according to ICD-10 procedure code assigned. d) inpatient admission – hospital cost for average Ontario hospital according to ICD-10 procedure code assigned. Data for the latter two categories will be obtained from the Ontario Case Costing Initiative ([www.occp.com](http://www.occp.com/)). If necessary, Hospital for Sick Children case costs per ICD-10 code will be used for uncommon diagnoses or procedures. Repeat hospitalizations and emergency department visits will be included. Followup clinic visits will be costed at a GP or specialist minor assessment fee as appropriate. Indirect and out-of-pocket costs will not be not included.

The cost of each surfacing will be based on itemized materials and labour contracts from playground suppliers plus labour costs paid by the Toronto District School Board and associated with installation. Maintenance costs will include annual costs of labour and supplies and will be provided yearly by the TDSB.

A decision analysis model will be used to compare the costs and outcomes of the two surfaces. Injury probabilities assigned to each surface will be based on injury rates observed in the trial. All costs will be expressed in 2004 Canadian dollars. A 10-year time horizon will be used. All costs beyond one year will be discounted at 3%. If one surface results in a better outcome at a lower cost, then the incremental cost savings in direct medical resource utilization per injury prevented will be reported. If one surface results in a better outcome at a higher cost, then the incremental cost per injury prevented will be calculated. Sensitivity analysis will be used to test the robustness of the result to variations in the underlying assumptions. The probability of health outcomes, cost of medical care for each health outcome, cost of intervention, and effectiveness of intervention will be varied over a clinically appropriate range using one-way sensitivity analysis.

The trial is being run from the Population Health Sciences program of the research institute at the Hospital for Sick Children. Accordingly, PhD trained health economists are available during data collection and analysis phases.

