## What are the proposed primary and secondary outcome measures?

### Primary Outcome Measure - Upper Extremity Fracture Rates

The primary outcome is an upper extremity fracture occurring on the school playground. The definition of an upper extremity fracture will be parental report of a physician’s diagnosis of ‘break’, ‘fracture’, or ‘dislocation’ in children who were x-rayed AND required a cast, splint or sling.

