### Primary Outcome Measure

Based on OSBIE data from 1999-2001 we estimate a baseline arm fracture (lambda zero) rate of 4 per 1000 student years. A clinically significant difference would be a halving of this rate to 2 per 1000 student years (lambda one). This is consistent with reports of sand having ½ to 1/6 the injury rate of other surfaces (14). Each school of 410 students provides 820 student years (y) of data over the two year study. Hayes’ method of sample size estimation for cluster randomization was used (25), where the number of clusters (c) per arm is:

Setting alpha = .05 and power at 80%,and k (coefficient of variation between clusters) at 0.2, we estimate that 17 clusters per arm or 34 schools in total will be required. 37 have been randomized so the study should have ample power. Ample power exists if the coefficient of variation is between 0.1 and 0.3 (see appendix).

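### The cost rule for office-only injuries has no item for the x-ray and immobilisation that the primary-outcome definition requires of a fracture

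*Protocol*

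**What the plan says.** The section *Will the trial address any economic issues?* introduces its medical unit costs with "Direct health care costs will be calculated from OHIP perspective as follows" and then sets four routes. No visit carries no cost. The office route is "physician office visit only – GP minor assessment fee". An ED visit is costed at an Ontario average according to the assigned ICD-10 procedure code. An admission is costed at "hospital cost for average Ontario hospital according to ICD-10 procedure code assigned".

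For later care, "Repeat hospitalizations and emergency department visits will be included", and "Followup clinic visits will be costed at a GP or specialist minor assessment fee as appropriate".

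The section *Primary Outcome Measure - Upper Extremity Fracture Rates* accepts a parent's report of a physician's diagnosis, but only "in children who were x-rayed AND required a cast, splint or sling".

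The section *How will the outcome measures be measured at follow-up?* plans to obtain health records, and to abstract diagnostic and procedure codes from them, for children who attended an ED or were admitted. It plans no such step for office care.

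**The concern.** The two rules do not fit together for one group of children: those whose fracture meets the outcome definition but who were never seen in an ED or admitted. The outcome definition says they had imaging and immobilisation. The cost rule prices a consultation and nothing else, although the analysis sets out to capture direct health care costs to the province.

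The omission falls on injuries that needed imaging or immobilisation, which is the kind of injury that one surface is hypothesised to prevent. Medical savings credited to the surface with fewer fractures would be too low. If that surface is also the cheaper one, the reported saving per injury prevented is too small. If it is the dearer one, the cost per injury prevented is too high.

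**Working it through.** The protocol states no dollar figure for the medical cost of a fracture, so there is none to reproduce. The check is a comparison of the rules, followed by an illustration of the possible size.

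**Comparison by setting, for a fracture that meets the outcome definition**

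- ED or ward: the cost depends on the procedure code, so treatment given at that contact can enter the cost.
- Office only: the cost is one assessment fee. X-ray and a cast, splint or sling are certain by definition, and neither has a cost item.
- Follow-up clinic visit, whatever the first setting: one assessment fee, GP or specialist. The outcome definition does not say whether imaging or cast work happens at these visits. If it does, there is no item for it.

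For an office-only fracture the error can therefore go only one way, towards understatement. For follow-up it is possible but not shown.

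**How many fractures are involved**

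The protocol says "we estimate a baseline arm fracture (lambda zero) rate of 4 per 1000 student years", a halving to 2 per 1000, and 820 student-years per school, with 19 Fibar and 18 sand schools. Taking sand as the arm with the halved rate:

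- Fibar: 19 × 820 × 0.004 = 62.3
- Sand: 18 × 820 × 0.002 = 29.5
- Total: about 92 fractures

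The protocol does not say how many of these would be treated only in an office.

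**Illustrative size (all inputs below are assumptions)**

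Express costs in multiples of the minor assessment fee. Let w be the office-only share, E the ED cost (5 to 20 fees), r the uncosted x-ray plus immobilisation (1 to 5 fees), and assume 2 follow-up visits at one fee each.

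- Cost under the protocol's rule = w + (1 − w)E + 2
- Cost with the missing items = w(1 + r) + (1 − w)E + 2
- Understatement = 1 − (first ÷ second)

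Results:

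- w = 0: 0%.
- w = 0.10, lowest (E = 20, r = 1): 1 − 20.1/20.2 = 0.5%. Highest (E = 5, r = 5): 1 − 6.6/7.1 = 7.0%.
- w = 0.50, lowest (E = 20, r = 1): 1 − 12.5/13.0 = 3.8%. Highest (E = 5, r = 5): 1 − 5.0/7.5 = 33.3%.

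If each follow-up visit also had uncosted services worth r/2, then even with w = 0 the understatement would run from 1 − 22/23 = 4.3% (E = 20, r = 1) to 1 − 7/12 = 41.7% (E = 5, r = 5). That depends wholly on follow-up services that the protocol does not describe.

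**The case against.** Much can be said in the plan's defence.

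- **Fractures in general.** A reader might infer that the cost of every fracture is understated. The protocol does not support that: initial ED and inpatient care is costed by procedure code, and repeat ED visits and admissions are counted separately. Only office-only care and follow-up clinic visits fall under the assessment-fee rule. The office-only group may be close to empty.
- **Follow-up.** The definition requires an x-ray and a cast, splint or sling once. A sling involves no cast change. Omitted cost at follow-up is plausible but not established.
- **Sensitivity analysis.** The protocol says that "cost of medical care for each health outcome, cost of intervention, and effectiveness of intervention will be varied over a clinically appropriate range". Upward variation would test this uncertainty. It does not correct the base case, and the range is not given.
- **Detail of fee codes.** Itemised fees are often left to an analysis plan. Here, however, the protocol fixes the fee for the office route, and following it as written produces the omission.

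A further tempting inference is that a small omission could reverse the economic conclusion. Table 1 gives a re-surfacing gap of 7073.68 − 5688.9 = $1,384.78 per school. At the planning rates, 410 × 0.002 = 0.82 fractures are prevented per school-year, or 8.2 over the 10-year horizon. The gap divided by 8.2 is $169 per prevented fracture (about $192 with 3% discounting after the first year: 1384.78 ÷ (0.82 × 8.786)). This is only the omission whose total equals the gap. Let c be the cost already captured per prevented fracture. With an omission of $169, the true net saving is 8.2(c + 169) − 1385, or about 8.2c, and the calculated one is about 8.2(c − 169). The sign changes only if c is itself below $169 (about $192 discounted), Fibar is the safer surface, and maintenance costs are ignored, although the protocol includes them. Nothing in the protocol supports so low a captured cost. The $169 is also an average over all prevented fractures: if 10% were office-only and follow-up is set aside, each would need about $1,690 of omitted services (169 ÷ 0.10). Finally, the planning hypothesis favours sand, which is also cheaper to install. In that case, on installation cost, the omission shrinks a saving without changing which surface is preferred.

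**Conclusion.** The point holds in a limited form. The office-only cost rule omits services that the protocol's own outcome definition makes certain, and it prices the same fracture on a different basis from the ED and inpatient routes. The direction is known: the direct medical cost of office-only fractures is understated. Follow-up clinic visits have the same gap if imaging or cast work takes place there.

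The size is unknown and may be small. The percentages above rest on assumed fee ratios, visit counts and office-only shares, and show only how the effect grows with those inputs. No reversal of the economic conclusion is claimed. The primary comparison, the secondary outcomes and the sample size are not affected. This is a worthwhile improvement confined to the economic analysis.

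**What to change.** In the economic section, change category (b) to the assessment fee plus the provincial fees for x-ray and for application of a cast, splint or sling, whenever the parent interview records them. The interview must already establish both in order to apply the outcome definition, so the initial visit needs no new data.

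For follow-up clinic visits, add the fees for any imaging or cast procedure reported. Where these are not reported, state an assumed number per fracture and vary it in the planned one-way sensitivity analysis.

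The cost is a few more lines in the fee table and, for follow-up, one explicit assumption that may be imprecise.

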## What is the allocation method?

A computer generated random number list was used to assign the 37 participating schools to Fibar® or granite sand groups. School level covariates including student population, socioeconomic status, and playground size are balanced between the groups as shown in table 1 below:

Table 1: Results of Randomization:

|  | **Fibar Schools**  **N = 19**  **Mean (S.D.)** | **Granitic Sand Schools**  **N = 18**  **Mean (S.D.)** | **P-Value** |
| --- | --- | --- | --- |
| Number of Students | 409.2 (312.1) | 416.3 (195.4) | 0.934 |
| Learning Opportunities Index (LOI) | 0.55 (0.27) | 0.49 (0.29) | 0.533 |
| Size of Playground (m2) | 18826.6 (22657.1) | 17142.8(22589.3) | 0.835 |
| TDSB Budget ($) | 42914.6 (31086.8) | 48658.70 (27426.2) | 0.555 |
| Cost of re-surfacing ($) | 7073.68 (1442.55) | 5688.9 (1179.9) | 0.003 |

Note: The TDSB Learning Opportunities Index 2002-03 combines information from the following variables: average and median income of families with school-aged children; parental education; proportion of lone-parent families; recent immigration; housing type (apartment, single detached housing); student mobility. It is the standard socioeconomic status measure for TDSB schools.

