# Details of the Trial Team

## Trial Management

### Timelines

Random allocation of intended surfaces to schools occurred in the spring of 2003. HSC ethics review board approval for the study has already been obtained. School playground replacement began in the summer of 2003 and will be completed at all schools in the spring of 2004. The service life of each playground is estimated at 20 years. Data will be collected during two complete school years once funding is received. Data analysis will occur during the three months following completion of data collection.

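### When one surface is both safer and cheaper, the economic rule reports medical savings per injury prevented, which omits surfacing costs and does not show how many injuries were prevented

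*Protocol*

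**What the plan says.** The section of the protocol on economic issues plans an analysis from the provincial government's perspective, on the ground that "both direct health care costs and education funding fall under the jurisdiction of the provincial government". Health care is costed by level of care. On the other side of the ledger, "The cost of each surfacing will be based on itemized materials and labour contracts from playground suppliers", to which school board installation labour and yearly maintenance costs are added. A decision model then compares the two surfaces on costs and outcomes.

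Two reporting rules follow. The first opens "If one surface results in a better outcome at a lower cost" and continues "then the incremental cost savings in direct medical resource utilization per injury prevented will be reported". The second reads "If one surface results in a better outcome at a higher cost, then the incremental cost per injury prevented will be calculated".

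Table 1, in the section on the allocation method, gives for Fibar and sand in turn: "Cost of re-surfacing ($) | 7073.68 (1442.55) | 5688.9 (1179.9) | 0.003".

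**The concern.** The two rules use different numerators. In the better-but-dearer case the numerator is incremental cost, which under the stated perspective means all the costs collected. In the better-and-cheaper case it is medical cost only. Installation and maintenance, which the perspective brings in and which help to decide which rule applies, drop out of the figure that is reported.

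The form of the figure is also a problem. A saving in medical cost divided by the number of injuries avoided is a unit cost of the avoided injuries. A school board or standards committee choosing a surface needs to know how much money is saved in total and how many injuries are avoided, and this ratio gives neither.

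**Working it through.** **Inputs.** From the protocol: 410 students per school and a 10-year horizon; 3% discounting of costs; all injuries at 15 per 1000 student-years with a 33% reduction planned; arm fractures falling from 4 to 2 per 1000; re-surfacing costs from Table 1. Assumed, because the protocol gives none: mean medical cost per injury of $500 (range $200 to $2,000) and no difference in maintenance cost.

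**The plan's own figures.** The economic section states no result to reproduce. The injury rates can be checked through the sample size. With c = 1 + (1.96 + 0.84)² × [(λ0 + λ1)/y + k²(λ0² + λ1²)]/(λ0 − λ1)², y = 820 and k = 0.2, the primary outcome (4 vs 2 per 1000) gives 16.93, so 17 per arm, and the secondary (15 vs 10 per 1000) gives 14.65, so 15 per arm. Both agree with the protocol.

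**Step 1: what the ratio is.** Let r0 and r1 be the injury rates, and c0 and c1 the mean medical cost per injury, on the worse and the better surface. The reported figure is

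R = (r0·c0 − r1·c1)/(r0 − r1),

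the mean medical cost of the prevented injuries. If c0 = c1 = c, then R = c for any r0 and r1.

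**Step 2: number prevented.** The re-surfacing difference is 7,073.68 − 5,688.90 = $1,384.78 per school, or 19.6% of the Fibar cost. Ten annual payments discounted at 3% from year 0 sum to 8.786. At a 33% reduction, injuries prevented per school are 410 × 0.015 × 0.33 × 10 = 20.3. The medical saving is 410 × 0.015 × 0.33 × 500 × 8.786 = $8,916, and $8,916/20.3 = $439. Adding re-surfacing gives $10,300.

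| Reduction | Injuries prevented per school | Medical saving per injury prevented | Total saving per school | Total saving per injury prevented |
|---|---|---|---|---|
| 5% | 3.1 | $439 | $2,736 | $890 |
| 33% | 20.3 | $439 | $10,300 | $508 |
| 50% | 30.8 | $439 | $14,893 | $484 |
| 80% | 49.2 | $439 | $22,999 | $467 |

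If injuries are discounted like costs, the third column is $500 throughout; it is constant either way. At 33% and unit costs of $200 to $2,000, the medical ratio runs from $176 to $1,757 and the total saving from $4,951 to $37,048.

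**Step 3: what is left out.** Re-surfacing is 1,384.78/10,300 = 13% of the total saving at 33% and $500, 28% at $200 and 4% at $2,000. The sign can also change. If Fibar proved safer by the same 33%, the total saving would be 8,916 − 1,385 = $7,531. That is still the better-and-cheaper branch, and the reported figure would again be $439.

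**Step 4: a shift in case mix.** The planning rates imply other injuries falling from 15 − 4 = 11 to 10 − 2 = 8 per 1000. With assumed costs of $2,000 per fracture and $200 per other injury, the mean cost is (4 × 2,000 + 11 × 200)/15 = $680 on the worse surface and (2 × 2,000 + 8 × 200)/10 = $560 on the better. The ratio is (2 × 2,000 + 3 × 200)/5 = $920. With other injuries kept at 11 to 8, it is $457 if fractures fall to 3.5 per 1000 and $1,100 if they fall to 1. If both types fall by the same proportion p, it is (4 × 2,000 + 11 × 200)p/(15p) = $680 for every p.

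**The case against.** A reader might go further in several ways that the protocol does not support.

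- **That the ratio is simply the average medical cost of an injury and carries nothing about the effect.** This is exact only if mean cost per injury is equal in both arms. The protocol plans a 50% fall in fractures and 33% in all injuries, so case mix should shift. Step 4 shows the ratio then reflects which injuries are prevented. What cancels is the number prevented under proportional reductions.
- **That surfacing costs are ignored.** They are collected, enter the decision model, are varied in sensitivity analysis, and presumably help to decide which rule applies. They are missing only from the figure prescribed for this branch. Nothing forbids reporting total cost beside it, but nothing requires it.
- **That the protocol expects sand to be safer and cheaper.** The research question is non-directional, and the background notes that mechanical tests favour wood fibre. Only the re-surfacing difference is documented; the section on co-interventions says maintenance may differ but gives no amount.
- **That a 10-year horizon conflicts with the asset's life.** The timelines section does say "The service life of each playground is estimated at 20 years", but the section on why a trial is needed now gives 10 to 20 years, so the horizon lies within the protocol's own range.
- **That injuries will be left undiscounted.** The protocol is silent on this, and an analysis plan may settle it.

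It is also fair to say that this is an ancillary analysis. What stands against all of this is the wording of the better-and-cheaper rule itself, which fixes a medical-only numerator that the companion rule does not use.

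**Conclusion.** The point holds in a limited form. Followed as written, the better-and-cheaper rule yields a figure that departs from the stated perspective, does not match the companion rule, and cannot show how many injuries were prevented when all types fall in proportion. The documented omission is $1,384.78 per school on re-surfacing, plus a maintenance difference of unknown size and sign. As a share of the total saving it is about 4% to 28% at the planned 33% reduction. Those shares rest on the assumed range of unit costs and on equal maintenance costs. The branch is plausible, given Table 1 and the lower injury rates on sand cited in the sample size section, but it is not established. The matter is minor: it affects the reporting of the economic analysis and leaves the design, the data and the injury comparisons as they are.

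**What to change.** Reword the better-and-cheaper rule. In that case, state that the surface dominates, and report two separate quantities per school: incremental total cost (installation, maintenance and health care) and injuries prevented. Give each an interval that respects randomization by school, for example by resampling schools within arm. These replace the medical-only ratio. Merely widening its numerator to total savings would not do: in the last column of the table the ratio falls from $890 to $467 as the surface becomes safer, so a better result looks worse. Keep incremental cost per injury prevented for the better-but-dearer case.

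The cost is a few sentences in the economic section and slightly more reporting. All the inputs are already to be collected.
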